### Data collection methods

Diet will be assessed using a validated questionnaire known as CADET (Child And Diet Evaluation Tool). CADET has been validated in an ethnically diverse population [42] and has been used to evaluate the ‘National Free School Fruit Scheme’ in primary school children [43,44] and has also been used in a large national randomised controlled trial of an intervention to maintain fruit and vegetable eating in Year 3 children once they are no longer eligible for free fruit [45]. Measures of socio-economic position are also included on the CADET. This includes a record of postcode, ethnic background and highest educational level of parents – these questions to be completed by the parent.

### Dietary assessment method: school and home food diaries

For this trial diet will be assessed using a modified version of the CADET questionnaire. To complete the School and Home Food diary participants tick each item consumed, under the appropriate meal time heading within the 24-hour period. The School Food Diary will be completed by an administrator at school for all school time meals, and then the children are given the Home Food Diary to take home and record for their evening snacks and meals, as well as breakfast the next day. The Home Food Diary is to be completed by a parent or carer. The following day the administrator will go back to the school to collect the Home Food Diary, and check that it has been completed accurately. If a child forgets to return their Home Food Diary a retrospective recall will be taken for all evening meals and breakfast by the administrator.

### Home food diary instruction DVD

To improve accuracy and completion of the Home Food Diary a short cartoon DVD was developed. Previously there were two pages of instructions for parents to read on how to complete the diary. The DVD was designed for children and parents to watch together before completing the Home Food Diary, with the aim of helping parents and children with low literacy ability or English as a second language to understand how to complete the diary.

### Knowledge and attitudes towards fruit and vegetables questionnaire

A short questionnaire to identify children’s knowledge and attitude towards fruit and vegetable consumption, and assess gardening activity levels will be administered in school. The knowledge questions assess children’s ability to recognise different fruit and vegetables. Children will be presented with a list of fruit and a list of vegetables (and a few herbs), with a colour picture for each, and they have to draw a line connecting the name with the right picture. The attitude questions are based on previously validated research by Somerset and Markwell, 2009 [46]. The gardening questions assess the children’s gardening experience; what they have grown and what they have tasted. This questionnaire will be read out to the children as a class, to help them with any difficult words. Children will complete the questionnaire individually.

### Process measures

Process evaluations are useful to identify adherence level to the intervention for each school. At baseline and follow-up, schools will be asked a set of gardening questions which are based on the RHS school bench marking system that ranks schools on their gardening activity levels from 1–5. An email consisting of different questions about gardening activities within the school, will be sent to the class teacher to capture what fruit and vegetables each school grows and harvests. This information will be captured via email in October 2010 for trial year one and October 2011 for trial year two. For the intense intervention trial schools in trial one, additional details regarding the intervention activities within each school will be captured by the regional advisor. For the less intense intervention, level of involvement in the twilight sessions for both trials one and two will be recorded. The regional advisor will keep a record of teacher’s attendance. The nature of this type of intervention allows schools to naturally tailor it to their individual needs. By monitoring what activities are undertaken in the school garden and in the classroom, there is an opportunity to explore how intervention elements might be associated with dietary change.

### Assessment and follow up

All measures will be taken at baseline and then at the end of the intervention, after two growing seasons e.g. within 15–17 months after baseline measurements were collected. Schools will have baseline measures taken when children are in the Spring Term of Year 3 and 4 (2010) and then again when these children are in Years 5 and 6, in the Autumn Term of that year (2011). The RHS Campaign will take place in schools over two growing seasons which will include the summers of 2010 and 2011. Support will be provided throughout the year to schools by the regional advisor.

### Study interventions

The RHS Campaign for School Gardening consists of two programmes. For the intensive intervention the schools known as Partner Schools receive the following:

· A day visit from the RHS regional advisor each half term to work in the garden with teachers and children (Summer Term 2010 to Summer Term 2011 inclusive).

· Follow up visits to aid lead teachers with planning (Autumn Term 2010 to Autumn Term 2011)

· General ongoing advice on the school garden, free seeds and tools

· 1 twilight teacher training session each term (Summer term 2010 to Summer term 2011 inclusive), based on seasonal tasks in the school garden (open to Partner School teachers and others from local schools)

· Free access to a wide range of teacher resources at http://www.rhs.org.uk/schoolgardening/

The role of the regional advisor is to assist the schools to develop a successful garden, through working directly with teachers and pupils to give them support and practical advice. They are also charged with helping schools overcome particular barriers to developing gardening within schools. Regional advisors have the expertise and experience to tie in gardening and growing activities with the National Curriculum and to run staff training sessions for teachers.

The less intensive intervention schools known as Associate Schools will work with the RHS by attending twilight training once a term at their nearby Partner school, to help support them in developing and using their school garden. Unlike the Partner Schools the Associate schools will not have direct support from the regional advisor. The regional advisor will be running these twilight sessions for them and provide the Associate Schools with advice as needed for their school garden.

Trial One consists of schools participating in both intervention groups mentioned above, whereas for Trial Two schools involved in the less intensive intervention/Associate Schools and a group of control schools are included. These control schools will not receive any support from the regional advisor during the period of the trial, they will however, be eligible for associate intervention at the end of the study. However, it is recognised that most schools will be engaging in some activity around this topic. Baseline evaluation of all schools will assess the level of active engagement with growing by these schools.

### Proposed outcome measures

#### The primary outcome measure will be the following

· Food:

· Daily portions of fruit and vegetable intake at follow-up (15 months after baseline)

· Daily portions of fruit intake

· Daily portions of vegetable intake

The effectiveness of either intervention would be determined by an increase in mean intake in one of the following: mean intake of fruit, mean intake of vegetables, or mean intake of fruit and vegetables at follow-up after adjusting for baseline

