## Research questions

The following research questions apply to both Trials 1 and 2:

· Can the RHS Campaign lead to increases in vegetable and fruit intake in children aged 8–9 years?

· Does the RHS Campaign affect children's intake of other food and drink e.g. savoury snacks, confectionery products, soft drinks?

· What is the effect of the RHS Campaign on intake of key nutrients (fat, carbohydrate, protein, vitamin C, carotene, iron, sodium, folate)?

The effectiveness of either intervention would be determined by an increase in mean intake in one of the following; mean intake of fruit, mean intake of vegetables, or mean intake of fruit and vegetables at follow-up after adjusting for baseline.

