### Proposed sample size

Cluster randomisation will be used, randomising at the school level, because the intervention will involve whole schools and participating classes. Based on results from our previous work on schools in a national sample, we estimate the standard deviation for the amount of vegetables eaten to be 85 g and for fruit 143 g. The associated intraclass correlation coefficient for total vegetables from Project Tomato was 12.5% and for fruit 11.4% (unpublished results). This sample of 50 children (one year 3 class and one year 4 class) from each school, will give a design effect of approximately 6.6 for vegetables and 7.1 for fruit to take account of the cluster randomisation. To have 90% power to detect a 0.5 portion difference in vegetable intake, 627 per group are required, i.e. about 13 schools using 2 classes from each school. To have 90% power to detect a 1 portion difference in fruit intake, 482 per group are required, i.e. about 10 schools. Based on results from our evaluation of the School Fruit and Vegetable Scheme, 75% who completed the Child And Diet Evaluation Tool (CADET) at baseline also completed the final follow up CADET. To allow for this margin of safety, 16 schools per group will be selected in each group apart from the intensive intervention group where it is only possible for 10 schools to be involved. The size of effect the study is powered to detect, (one half of a portion of vegetables or one portion of fruit) was chosen because it was considered the smallest improvement in intake that was worthwhile detecting with the achievable sample size, and considering the nature of the intervention.

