### Secondary outcome analysis of the trial

To formally compare sub-groups, two predefined individual level variables (with interaction term) will be added one at a time, namely gender and ethnicity a p value of 0.01 will be used to take into account multiple testing. These will answer plausible questions, i.e. that the effect of the intervention differs by gender or by ethnicity. Unadjusted analyses originally performed in MLwiN will be repeated in Stata 10[39] using fixed effect Sandwich estimates to take account of the cluster randomisation to assess robustness of conclusions. These are exploratory analyses that are hypothesis generating.

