### Multiple comparisons

No adjustment will be made for multiple comparisons of these pre-specified secondary analyses. All tests will use a 1% significance level, and report 95% confidence intervals.

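### Each trial counts as a success if any one of three primary outcomes rises, with no error control stated for that rule and no significance level written for the primary tests

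*Protocol article*

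**What the plan says.** Under Proposed outcome measures the protocol lists three primary outcomes: daily portions of fruit and vegetables together, of fruit, and of vegetables. The success rule follows: "The effectiveness of either intervention would be determined by an increase in mean intake in one of the following". The Research questions section repeats it for both trials, naming "mean intake of fruit, mean intake of vegetables, or mean intake of fruit and vegetables at follow-up after adjusting for baseline". Neither place ranks the outcomes, divides alpha between them or says what counts statistically as an increase.

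The Multiple comparisons section reads: "No adjustment will be made for multiple comparisons of these pre-specified secondary analyses". It goes on: "All tests will use a 1% significance level, and report 95% confidence intervals". The section on secondary outcome analysis says of the gender and ethnicity interactions that "a p value of 0.01 will be used to take into account multiple testing", and the Subgroup analyses section also sets 1%.

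Proposed sample size treats two of the three outcomes separately: "To have 90% power to detect a 0.5 portion difference in vegetable intake, 627 per group are required", and "To have 90% power to detect a 1 portion difference in fruit intake, 482 per group are required". It names no alpha and gives no calculation for the combined outcome.

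**The concern.** A rule that is met by any one of several tests has a higher false-positive rate than each test alone. If each test is run at the level the sample size seems to assume, a programme with no effect is called effective more often than that level suggests. This rule decides the headline conclusion of both trials. The multiplicity paragraph does not help, because it deals with secondary analyses, and its reference to all tests leaves the level for the primary tests open to two readings.

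**Working it through.** **Inputs.** From Proposed sample size: SD 85 g (vegetables) and 143 g (fruit); intraclass correlation 0.125 and 0.114; design effect 6.6 and 7.1; 50 children per school; 75% retention; 16 schools per group, 10 in the intensive group. Assumptions: a portion is 80 g, so the target differences are 40 g and 80 g; combined intake is the sum of the two; an increase means a statistically significant one.

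**1. Which alpha do the sample sizes imply?** Children per group = 2 × [SD × (z for alpha + z for power) / difference]² × design effect, with 90% power.

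- Vegetables, two-sided 5%: 2 × [85 × (1.960 + 1.282) / 40]² = 94.9, rounded up to 95; 95 × 6.6 = 627. Stated: 627.
- Fruit, two-sided 5%: 2 × [143 × (1.960 + 1.282) / 80]² = 67.15, rounded up to 68; 68 × 7.1 = 482.8. Stated: 482.
- Other levels miss: one-sided 5% gives 515 and 391, two-sided 1% gives 891 and 682, one-sided 1% gives 779 and 596.

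So, with an 80 g portion, both figures were planned at two-sided 5%.

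**2. Error rate of the rule.** Under no effect, draw z for vegetables and for fruit with correlation r, and set z for combined = (85 × z veg + 143 × z fruit) / √(85² + 143² + 2 × r × 85 × 143). Count the draws in which at least one of the three is significant (4 million draws).

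| r | any significant, 5% per test | any significant increase, 5% per test | any significant, 1% per test |
|---|---|---|---|
| -0.2 | 11.6% | 6.0% | 2.5% |
| 0 | 11.3% | 5.7% | 2.5% |
| 0.2 | 10.8% | 5.4% | 2.3% |
| 0.4 | 10.0% | 5.0% | 2.2% |
| 0.7 | 8.6% | 4.3% | 1.9% |
| 0.9 | 7.1% | 3.5% | 1.5% |

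A single test would give 5%, 2.5% and 1%. The relevant r is that between the two effect estimates. With 37.5 to 50 children per school, between-school variation makes up about 83 to 88% of each estimate's variance: ICC / [ICC + (1 - ICC)/m], for example 0.125 / (0.125 + 0.875/37.5) = 84%. The school-level correlation therefore dominates. The protocol does not give it, so the whole range is shown.

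**3. Power at the stated sizes if 1% governed the primary tests.**

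- Vegetables: SE = 85 × √(2 × 6.6/627) = 12.33; 40/12.33 = 3.24; 3.24 - 2.576 = 0.67, power 75%.
- Fruit: SE = 143 × √(2 × 7.1/482) = 24.55; 80/24.55 = 3.26; 3.26 - 2.576 = 0.68, power 75%.

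**4. Cost of Holm.** Its strictest step is 0.05/3 = 1.67%, with z = 2.394. With 75% retention, 37.5 children per school remain, and the design effect is 1 + 36.5 × ICC: 5.56 for vegetables and 5.16 for fruit. Trial 2 has 600 against 600 children, Trial 1 375 against 600.

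| | SE | difference/SE | power at 5% | power at 1.67% |
|---|---|---|---|---|
| Vegetables, Trial 2 | 11.57 | 3.46 | 93% | 86% |
| Vegetables, Trial 1 | 13.20 | 3.03 | 86% | 74% |
| Fruit, Trial 2 | 18.76 | 4.27 | 99% | 97% |
| Fruit, Trial 1 | 21.39 | 3.74 | 96% | 91% |

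Under no effect, testing all three at 1.67% gives a familywise error of 4.1% at r = -0.2 down to 2.5% at r = 0.9.

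One side observation: at 50 per school the stated intraclass correlations give 1 + 49 × 0.125 = 7.1 for vegetables and 1 + 49 × 0.114 = 6.6 for fruit, the reverse of the protocol. Step 1 uses the stated values because they reproduce the stated sizes. Step 2 does not depend on them.

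**The case against.** The strongest counter-argument is the sentence about the 1% level. Taken literally, all tests include the primary ones, and the protocol elsewhere uses 0.01 as its device against multiple testing. The error of the rule would then be about 1.5 to 2.5%, below 5%. This reading cannot be excluded, so the documents do not support the flat statement that the false-positive rate is doubled. Context is against it: the sentence sits in a paragraph about secondary analyses, beside 95% intervals, and the other two mentions of 1% concern subgroup tests. It would also contradict the 90% power claim at the stated sizes.

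The 5% level itself depends on the portion weight. A portion of about 95 g at two-sided 1% would give nearly the same group sizes (about 629 and 479 before rounding). The inference is reasonable but not proved.

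A reader might go further in three ways that do not hold. Three independent tests would give 1 - 0.95³ = 14.3%, but combined intake is the sum of the other two, so the inflation is smaller. The words "No adjustment will be made for multiple comparisons" might be taken as a refusal to adjust the primary outcomes, but the sentence continues and limits itself to secondary analyses. And adding up error over the two trials is not needed, since they ask different questions; the per-trial figure is the relevant one.

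Finally, an analysis plan not shown here could set the primary level and an adjustment. That is fair for detail. But the protocol itself fixes the success rule, states it twice, and has its own multiplicity section that does not reach it.

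**Conclusion.** The point stands in a bounded form. The rule for declaring effectiveness is explicit, can be met by any of three outcomes, and has no error control stated for it; the primary alpha is not written. On the more natural reading, two-sided 5% per test, the familywise error per trial is about 10 to 12% for correlations from -0.2 to 0.4 and 7.1% at 0.9, and false claims of an increase occur about 3.5 to 6% of the time against 2.5%. Roughly double is right at low to moderate correlation and too strong at high correlation (1.4 times at 0.9). On the 1% reading the error is controlled but the power statement fails. Either way one statement in the protocol has to change. The figures rest on the 80 g portion, on combined intake being the sum of the other two, and on an unknown correlation.

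**What to change.** Three wording changes and one restatement:

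- State that the primary tests use an overall two-sided 5% in each trial.
- Limit the 1% sentence in Multiple comparisons to secondary and subgroup tests.
- In both places where the rule appears, require an increase in at least one of the three outcomes that is significant after Holm adjustment across the three.
- Restate power. For vegetables (0.5 portion) at the strictest step it is about 86% in Trial 2 and 74% in Trial 1, against 93% and 86% unadjusted. For fruit (1 portion) it is about 97% and 91%. State the portion weight in grams.

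No further schools or data are needed; the price is the loss of vegetable power, mainly in Trial 1.

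Making combined intake the sole primary outcome, with fruit and vegetables claimed only if it is significant, is an option but not the first choice. It keeps the full 5%, but the protocol has no sample size for that outcome. Assuming a combined SD of 166 to 193 g (correlation 0 to 0.4), an intraclass correlation of 0.12 and 75% retention, a vegetable-only gain of 0.5 portion would pass that gate with power of only about 34 to 44% in Trial 2 and 27 to 35% in Trial 1.

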#### Secondary outcomes will be the following

· Nutrient:

· Total energy intake (MJ/day)

· Fat intake (g/day)

· Saturated fat (g/day)

· Salt intake (g/day)

· Sugars (g/day) including non milk extrinsic sugars

· Carotene intake (mg/day)

· Vitamin C intake (mg/day)

· Vitamin D intake (mg/day)

· Iron (μg/day)

· Fibre (g/day)

· Zinc (μg/day)

· Carbohydrates (g/day)

· Folate (μg/day)

· Foods:

· high in fat, salt or sugar and sugar sweetened beverages

· Behavioural:

· Children’s attitude to fruit and vegetable consumption

· School level:

· Involvement of schools in promoting consumption of fruit and vegetables (number of lessons devoted to school gardening and growing or learning about fruit and vegetables, school food policy, involvement in other national/local food related initiatives).

· Involvement by schools of parents in promoting consumption of fruit and vegetables among pupils.

· Process measures concerning the practicality of the intervention, timing, delivery, used and not used elements of the intervention.

### Statistical analysis

Baseline child-level variables between the two intervention groups will be assessed for the following variables:

School level:

· % children with English as an additional language

· % non-white children

· % children with free school meals eligibility

· % children defined as having special educational needs

Child level:

· Sex

· Age

· Each of the primary and secondary outcomes

### Primary analyses

A random or fixed intercepts model of primary and secondary outcomes will be used allowing for hierarchical structure of data caused by cluster randomisation: child within class within school. MLwiN [47] will be used for this analysis. The single covariate for the intervention group will be included in the model (treated as a random effect since schools in the trial are themselves a random sample from the population of schools).

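### The primary model as written has intervention group as its only covariate, while effectiveness is defined on intake adjusted for baseline

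*Protocol article*

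**What the plan says.** Under Proposed outcome measures, either intervention counts as effective if there is an increase in "mean intake of fruit, mean intake of vegetables, or mean intake of fruit and vegetables at follow-up after adjusting for baseline". The Research questions section gives the same definition.

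The Primary analyses section describes a multilevel model, "allowing for hierarchical structure of data caused by cluster randomisation: child within class within school", fitted in MLwiN. On covariates it says: "The single covariate for the intervention group will be included in the model". It mentions no other term.

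Three further places bear on the point:

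- Statistical analysis lists each primary and secondary outcome among the baseline variables, but only for comparison between groups: "Baseline child-level variables between the two intervention groups will be assessed for the following variables".
- Secondary outcome analysis of the trial says: "Unadjusted analyses originally performed in MLwiN will be repeated in Stata 10".
- Assessment and follow up shows that the baseline values will exist: "All measures will be taken at baseline and then at the end of the intervention, after two growing seasons".

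**The concern.** The definition of success and the primary model do not match. One requires a baseline adjustment; the other limits the covariates to one, and that one is the arm. An analyst who follows Primary analyses to the letter obtains an unadjusted difference at follow-up. An analyst who follows the outcome section fits a different model.

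Two things are at stake. The first is precision and balance: there are few schools and intake is clustered within them, so baseline differences between arms arise easily by chance, and a baseline measurement already planned would go unused. The second is discretion: success may be declared on any one of three intake measures, and an open choice between adjusted and unadjusted results adds another option that could be settled after the results are known.

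**Working it through.** **Inputs from Proposed sample size.** Vegetables: SD 85 g, ICC 0.125. Fruit: SD 143 g. 50 children per school; stated design effects 6.6 (vegetables) and 7.1 (fruit); 90% power; targets 0.5 portion of vegetables and 1 portion of fruit; 75% completing follow-up, so 37.5 children per school. Schools: 10 v 16 in Trial 1, 16 v 16 in Trial 2.

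**Assumptions not in the document.** 80 g per portion (0.5 portion = 40 g); two-sided 5% test; equal SDs at both times; baseline to follow-up correlation rs = 0.3 to 0.7 between schools and ri = 0.2 to 0.3 between children within schools; normal approximation.

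**1. The plan's own figures.** n per group = 2 × [SD × (1.96 + 1.2816) / target]² × design effect.

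- Vegetables: 94.9 × 6.6 = 626 (stated 627).
- Fruit: 67.1 × 7.1 = 477 (stated 482).

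Both agree closely without any baseline-correlation term. The sample size therefore does not depend on adjustment.

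**2. Chance imbalance in baseline vegetables.** SD of the difference = 85 × √[(0.125 + 0.875/50) × (1/k1 + 1/k2)].

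- Trial 1: 85 × √(0.1425 × 0.1625) = 12.9 g; 95% range ±25.4 g = ±0.32 portions.
- Trial 2: 85 × √(0.1425 × 0.125) = 11.3 g; 95% range ±22.2 g = ±0.28 portions.

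This is the imbalance at baseline, not the error in the result. At rs of 0.3 to 0.7, about 0.3 × 0.32 to 0.7 × 0.32, or ±0.10 to ±0.22 portions, would carry to follow-up in Trial 1.

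**3. Unadjusted power for vegetables, after loss to follow-up.** Variance factor = 0.125 + 0.875/37.5 = 0.1483. Power = Φ(40/SE − 1.96).

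- Trial 1: SE = 85 × √(0.1483 × 0.1625) = 13.2 g; power 86%.
- Trial 2: SE = 85 × √(0.1483 × 0.125) = 11.6 g; power 93%.

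**4. Adding the child's baseline value with one slope.** Most variation lies between children within schools, so the slope is close to ri. Variance ratio = [0.125 × (1 − 2·ri·rs + ri²) + 0.0233 × (1 − ri²)] / 0.1483.

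- rs 0.3, ri 0.2: (0.125 × 0.92 + 0.0233 × 0.96) / 0.1483 = 0.926, a 7% reduction.
- rs 0.7, ri 0.3: (0.125 × 0.67 + 0.0233 × 0.91) / 0.1483 = 0.708, a 29% reduction.

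Trial 1 SE falls to 12.7 g and 11.1 g; power 88% and 95%.

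**5. Adding the school mean baseline as well.** Each level then has its own slope. Variance ratio = [0.125 × (1 − rs²) + 0.0233 × (1 − ri²)] / 0.1483.

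- Low end: (0.125 × 0.91 + 0.0233 × 0.96) / 0.1483 = 0.918, an 8% reduction.
- High end: (0.125 × 0.51 + 0.0233 × 0.91) / 0.1483 = 0.573, a 43% reduction.

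Trial 1 power becomes 89% and 98%.

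**6. Sensitivity to the test level.** Multiple comparisons says that all tests use 1%. If that covers the primary analysis, replace 1.96 by 2.576: Trial 1 power is about 68% unadjusted and about 72% to 85% with one slope.

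**The case against.** The best defence is that adjustment is stated twice, once beside the primary outcome, and that the article condenses a fuller plan. The covariate sentence could then merely describe how the arm enters the model. That is a fair reading of intent, and it makes this a drafting conflict rather than proof that an unadjusted analysis was planned. It does not remove the conflict: condensing excuses an omission, whereas here two positive statements cannot both describe the primary analysis.

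A reader might take the word unadjusted in Secondary outcome analysis of the trial as confirmation that the primary model omits baseline. It does not settle the matter. The sentence follows the sex and ethnicity interaction terms, so it may mean without those terms. It may also pick out one subset of the MLwiN analyses, which would imply that adjusted ones exist too. The contradiction rests on the covariate sentence against the definition of effectiveness.

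A reader might also infer that the unadjusted model is biased or targets a different effect. Under randomisation, both linear models target the same mean difference. The chance imbalance that carries to follow-up is already inside the unadjusted standard error, so the unadjusted test remains valid. Setting ±0.32 portions beside the 0.5-portion target would therefore overstate the harm.

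**Conclusion.** The inconsistency is real and lies in the primary analysis. As written, the model does not yield the baseline-adjusted estimate that decides effectiveness, and the article does not say which result prevails. The loss is in precision, conditional balance and pre-specification, not in validity, and the stated sample size is not undermined.

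For vegetables in Trial 1, one child-level baseline slope would reduce variance by about 7% to 29% and raise power from about 86% to about 88% to 95%. Adding the school mean baseline would give about 8% to 43% and 89% to 98%. These ranges depend on the assumed correlations, the 80 g portion and the two-sided 5% level. The normal approximation is slightly generous: a t reference with 24 degrees of freedom lowers the 86% to about 83%. The contradiction itself depends on none of these assumptions. Severity: should be fixed.

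**What to change.** Restate the Primary analyses section along these lines: the primary model regresses follow-up intake on allocated arm, as a fixed effect, and on the child's baseline value of the same outcome, with random intercepts for class and school. The school mean baseline may be added; the upper part of the range above needs it. Label the model without baseline a sensitivity analysis, and say in Secondary outcome analysis of the trial which model is repeated in Stata.

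The cost is a few sentences, settled before outcome data are seen. No new data are needed, and the sample-size calculation can stand as far as this point is concerned.

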### Study population

#### Trial 1 inclusion criteria

All primary schools within the following London boroughs: Wandsworth; Tower Hamlets; Greenwich; and Sutton with classes in key stage 2 (years 3–6) will be invited to take part in the study.

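### The primary model makes the intervention term random and allows fixed intercepts; arm should be a fixed effect, with random intercepts for school and class

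*Protocol article*

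**What the plan says.** Under Primary analyses, the protocol article gives one model for all its outcomes, whether main or supporting: "A random or fixed intercepts model of primary and secondary outcomes will be used allowing for hierarchical structure of data caused by cluster randomisation". The levels are "child within class within school". The treatment term follows: "The single covariate for the intervention group will be included in the model", and it is to be "treated as a random effect since schools in the trial are themselves a random sample from the population of schools".

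Three other places bear on this:

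- Proposed sample size: "Cluster randomisation will be used, randomising at the school level". Arm is therefore constant within every school and every class.
- Proposed outcome measures: "The effectiveness of either intervention would be determined by an increase in mean intake in one of the following". The outcomes listed are mean intakes at follow-up, adjusted for baseline. Research questions says the same.
- Trial 1 inclusion criteria: all eligible primary schools in four named boroughs "will be invited to take part in the study". Trial 2 does the same in four further boroughs.

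**The concern.** The sentence attaches random status to the wrong term. If schools are regarded as drawn from a wider population, the school effect is random. The two arms are not drawn from a population of arms: they are the two conditions that the trial compares. The decision criterion is a difference in mean intake, which calls for a fixed contrast.

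The choice left open by "A random or fixed intercepts model of primary and secondary outcomes will be used" is the second problem. In a trial randomised by school, fixed intercepts for schools or classes absorb the whole between-school contrast, and that contrast is the treatment effect.

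The stated premise is also not borne out. Schools are invited by borough and then recruited, and no random sampling of schools is described. This changes no estimate, but it is the only reason given for the random term.

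At stake is the specification of the sole primary model. An analyst who follows the wording could reach different models, some of them unusable, and nothing elsewhere in the article settles which is meant.

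**Working it through.** **Inputs.** From Recruitment: Trial 1 has 10 and 16 schools, Trial 2 has 16 and 16. From Proposed sample size: vegetable SD 85 g, ICC 0.125, 50 children in two classes per school, 75% completing follow-up. Assumed, not in the document: 80 g per portion and a two-sided 5% level for the sample size.

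**1. The plan's own figures.** Per-group n before clustering is 2 × [SD × (1.960 + 1.282) / difference]².
- Vegetables: SD 85, difference 40 g, giving 94.9, rounded up to 95; 95 × 6.6 = 627, as stated.
- Fruit: SD 143, difference 80 g, giving 67.15, rounded up to 68; 68 × 7.1 = 482.8, against 482 stated.

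The two assumptions therefore fit the plan's arithmetic. These figures do not depend on the wording at issue.

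**2. Fixed intercepts as dummies.** Rank of the design matrix with one intercept per school (or class) plus the arm indicator:

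| Trial | Intercepts | Columns | Rank |
|---|---|---|---|
| 1 (10 vs 16) | school | 27 | 26 |
| 1 (10 vs 16) | class | 53 | 52 |
| 2 (16 vs 16) | school | 33 | 32 |
| 2 (16 vs 16) | class | 65 | 64 |

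Each matrix is one rank short, so the arm effect is not estimable. This holds whatever the SD, ICC or portion size. With one common intercept plus arm the rank is 2 for 2 columns and arm is estimable, but that mean model by itself does nothing about the hierarchy.

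**3. Arm as a two-level random factor.** With observed difference d and standard error SE, restricted likelihood gives a predicted difference of d × max(0, 1 − SE²/d²).

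Trial 1 with 75% retention: 50 × 0.75 = 37.5 children per school, so 375 and 600 children. Design effect = 1 + 36.5 × 0.125 = 5.5625. SE = 85 × √[5.5625 × (1/375 + 1/600)] = 13.2 g.
- d = 40 g: 13.2²/40² = 0.11, a reduction of about 11%.
- d = 27 g: 13.2²/27² = 0.24, a reduction of about 24%.
- d up to about 13 g: predicted as zero.

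A simulation with all 50 children per school (200,000 draws of the difference in school means) gave:

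| True difference | Allocation | Mean prediction, arm random | Predicted as exactly 0 | SE, arm fixed |
|---|---|---|---|---|
| 40 g | 16 vs 16 | 36.4 g | 0.6% | 11.3 g |
| 40 g | 10 vs 16 | 35.4 g | 1.8% | 12.9 g |
| 20 g | 16 vs 16 | 14.2 g | 22% | 11.3 g |
| 20 g | 10 vs 16 | 13.5 g | 29% | 12.9 g |

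With arm fixed, the estimates averaged 40.0 g and 20.0 g.

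**4. Arm as a random coefficient across schools.** With a 0/1 arm indicator, the between-school variance is σ0² in one arm and σ0² + 2σ01 + σ1² in the other. Two variances cannot determine three parameters, so σ1² and σ01 are not separately identified. The fixed part is unaffected: in one simulated 16 vs 16 data set the mean difference was 34.7 g (SE 14.3) both with random intercepts alone and with an independent random slope added. The fit with a free covariance failed with a singular matrix.

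**The case against.** The best defence is that the intended model can be inferred. Arm is called a covariate, and the stated hierarchy has three levels with no arm level above school. In multilevel usage, a covariate treated as random is naturally a random coefficient: a mean effect plus variation across schools. Step 4 shows that the mean difference then survives, and setting the covariance to zero removes the identification problem. Compliance with good practice promises intraclass correlations from the multilevel analyses, which points to random school effects. Secondary outcome analysis uses the term fixed effect for a model with sandwich errors, so fixed intercepts need not mean school dummies. If it did, software would expose the collinearity at once.

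Most of this stands. It makes the two-level random factor the less plausible reading and limits the rank result to the dummy reading. It does not make the text correct. The reason given still concerns schools and not the intervention; the article does not say that a random coefficient is meant; and the fixed option remains undefined. The sandwich analysis is unadjusted and labelled exploratory, so it does not replace the primary model.

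A reader might infer that the trial cannot report the mean difference it was designed to estimate. The documents do not support that. Random intercepts are one of the permitted options, the target is stated as mean intake adjusted for baseline, and Multiple comparisons commits to 95% confidence intervals.

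**Conclusion.** The point holds as a misspecification of the only primary model, stated in the text and not corrected elsewhere in the article. Random status is attached to the intervention term for a reason that supports only random school intercepts, and an intercept option is allowed that makes the effect inestimable if it means school or class dummies.

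The size depends on the reading. Under dummies, the loss of the effect is exact and needs no assumptions. Under a random coefficient, the mean difference is intact and only the variance parameters are poorly defined. The shrinkage of 11% at 40 g and 24% at 27 g applies only to Trial 1 under the two-level random-factor reading, with 37.5 children per school, SD 85 g and ICC 0.125; equating 40 g with half a portion also requires 80 g per portion. These percentages are not a forecast of bias in the trial.

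**What to change.** Rewrite the two sentences under Primary analyses to say that allocated arm enters as a fixed effect, that school and class enter as random intercepts, and that the baseline value of the outcome is included as a covariate, as Research questions and Proposed outcome measures require. Baseline should be named because the present sentence speaks of a single covariate. Delete the fixed-intercepts option. Attach the sampling rationale to the school intercept, worded as a working assumption, or drop it.

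The estimation method and reference distribution can be left to the analysis plan. The cost is about two sentences of wording; design, data collection and sample size do not change.
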